## Abstract

**Background:**

Venous thromboembolism comprising pulmonary embolism and deep vein thrombosis is a common condition with an incidence of approximately 1 per 1,000 per annum causing both mortality and serious morbidity. The principal aim of treatment of a venous thromboembolism with heparin and warfarin is to prevent extension or recurrence of clot. However, the recurrence rate following a deep vein thrombosis remains approximately 10% per annum following treatment cessation irrespective of the duration of anticoagulation therapy. Patients with raised D-dimer levels after discontinuing oral anticoagulation treatment have also been shown to be at high risk of recurrence.

Post thrombotic syndrome is a complication of a deep vein thrombosis which can lead to chronic venous insufficiency and ulceration. It has a cumulative incidence after 2 years of around 25% and it has been suggested that extended oral anticoagulation should be investigated as a possible preventative measure.

**Methods/design:**

Patients with a first idiopathic venous thromboembolism will be recruited through anticoagulation clinics and randomly allocated to either continuing or discontinuing warfarin treatment for a further 2 years and followed up on a six monthly basis. At each visit D-dimer levels will be measured using a Roche Cobas h 232 POC device. In addition a venous sample will be taken for laboratory D-dimer analysis at the end of the study. Patients will be examined for signs and symptoms of PTS using the Villalta scale and complete VEINES and EQ5D quality of life questionnaires.

**Discussion:**

The primary aim of the study is to investigate whether extending oral anticoagulation treatment (prior to discontinuing treatment) beyond 3–6 months for patients with a first unprovoked proximal deep vein thrombosis or pulmonary embolism prevents recurrence. The study will also determine the role of extending anticoagulation for patients with elevated D-dimer levels prior to discontinuing treatment and identify the potential of D-dimer point of care testing for identification of high risk patients within a primary care setting.

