## Methods

### Aims and objectives

Considering patients with a first unprovoked proximal DVT and PE who have been treated with 3–6 months oral anticoagulation, the aims of the study are:

•To investigate the effect of extending treatment with oral anticoagulation in terms of reduction in incidence of VTE and PTS

•To develop an algorithm to predict high/low recurrence rates in these patients

As part of this we will be investigating the following:

•To establish the performance characteristics of D-dimer testing whilst still on treatment as a prediction tool for recurrence of VTE in patients with first unprovoked proximal DVT or PE.

•To establish factors which contribute to the recurrence of VTE in patients with a first unprovoked proximal DVT or PE.

•To determine the cost-effectiveness of the measurement of D-dimer and subsequent extended treatment with anticoagulation.

•To determine patient preferences and utilities with regard to extended warfarin treatment.

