### Outcome measures

#### Primary outcomes

1. Number of recurrent thrombotic events between those with raised D-dimer at point of randomisation who were randomly allocated to the treatment arm (group RW) and those with raised D-dimer at point of randomisation who were randomly allocated to the no treatment arm and produced a normal D-dimer off treatment (NRO) and those with raised D-dimer at point of randomisation who were randomly allocated to the no treatment arm and then produced a raised D-dimer off treatment (RRO) (see Figure 1)

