**Figure 1 F1:**
[figure not shown]
Flow chart for trial intervention.

2. Number of recurrent thrombotic events between those showing an elevated D-dimer off treatment (RO) versus those showing a negative D-dimer off treatment (NO) (see Figure 1)

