Total sample size will be sufficiently large to show a significant difference in recurrence rates between those showing a positive D-dimer on treatment who receive warfarin (RW) and those showing a positive D-dimer who receive no treatment (RNO plus RRO). Following Palareti [7] this means a sample size for each group of 79 in order to give 90% power to a 5% significance test when comparing 2 year recurrence rates of 21.4% and 4.3%. Assuming a 50% positive D-dimer rate this implies a total of 79 × 2 × 2/0.9 = 352 patients taking part in the study (and 316 completing the study). Allowing a 50% participation rate this means that 704 patients need to be approached initially. With such a sample size an overall comparison of recurrence rates between the arms W and O can be made with power of between 86 and 99% assuming recurrence rates of between 1.4% and 4.3% for the warfarin arm (Group W, depending on what recurrence rate patients with normal D-dimer on warfarin produce) and 14.2% for the No treatment arm.

One of the objectives of the study is to determine an optimal cut off on a D-dimer result taken when the patient is receiving treatment. In a study of 272 patients, Baglin *et al.* report that 170/272 patients had a D-dimer in excess of 500 ng mL-1 and their ROC analysis suggests an optimal cut off of 500 ng/ml [10]. The circumstances of their study differ from ours but using their data will give some indication of the precision with which we will be able to estimate an optimal cut off with slightly more patients than Baglin *et al.* With some assumptions, a rough calculation of the precision with which a cut off in the region of 500 could be estimated with our sample size of 316 would be within about 7% (95% confidence interval).

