## Discussion

This study will primarily investigate the role of extending treatment with oral anticoagulation for those patients with raised D-dimer levels prior to discontinuing treatment and will study the impact of this management on both recurrence of thrombosis and development of post-thrombotic syndrome, both extremely costly outcomes for the NHS. This strategy would allow those people who require extended anticoagulation treatment to receive it whilst ensuring that those who only require short term treatment are not exposed to unnecessary and potentially dangerous treatment.

Identifying the potential for utilisation of D-dimer POC testing will make feasible the identification of those high risk patients within a primary care setting negating the necessity for costly and inconvenient referral elsewhere. Thus people with a first unprovoked proximal DVT or PE could be managed differently to current management with the potential for significant improvements in health outcomes and patient well being.

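### The article contradicts itself on its deciding comparison: the primary aim, the two primary outcomes and the sample-size contrast do not match

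*Protocol article*

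**What the plan says.** The article states its main question in several places.

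- **Abstract, Discussion:** "The primary aim of the study is to investigate whether extending oral anticoagulation treatment (prior to discontinuing treatment) beyond 3–6 months" prevents recurrence in first unprovoked proximal DVT or PE. This is W versus O in everyone randomised. The next sentence adds the elevated-D-dimer patients as a further question.
- **Aims and objectives:** again all patients: "To investigate the effect of extending treatment with oral anticoagulation in terms of reduction in incidence of VTE and PTS".
- **Discussion (main text):** "This study will primarily investigate the role of extending treatment with oral anticoagulation for those patients with raised D-dimer levels prior to discontinuing treatment".
- **Primary outcomes, item 1:** "Number of recurrent thrombotic events between those with raised D-dimer at point of randomisation who were randomly allocated to the treatment arm (group RW"), compared with NRO and RRO. Those are the Group O patients raised at randomisation, split by their later off-treatment D-dimer.
- **Primary outcomes, item 2:** "Number of recurrent thrombotic events between those showing an elevated D-dimer off treatment (RO) versus those showing a negative D-dimer off treatment (NO"). Both groups lie within Group O.
- **Sample size:** RW against the sum of RNO and RRO, with a group size of "79 in order to give 90% power to a 5% significance test when comparing 2 year recurrence rates of 21.4% and 4.3" per cent. It adds that "an overall comparison of recurrence rates between the arms W and O can be made with power of between 86 and 99" per cent.

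The coding in the same Sample size section, repeated under Abbreviations, defines RNO as normal at randomisation and raised only off treatment. The Analysis and statistical methods section lists types of method and does not say which comparison decides.

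**The concern.** These are not one question in different words. W versus O asks whether continuing warfarin works. RW against the raised part of Group O asks whether it works in raised-D-dimer patients. RO versus NO asks whether D-dimer predicts recurrence in untreated patients, and it cannot show a treatment effect. The answers can differ, and the article does not say which of them the trial's conclusion rests on.

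A separate analysis plan may supply an order of testing or a split of alpha, and the absence of those from an article is not the point. The point is that the existing statements conflict. Any analysis plan would have to overrule either the abstract or the main Discussion, and either the listed primary outcomes or the sample-size contrast.

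**Working it through.** **1. The statements side by side**

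| Place | Contrast | Is it W versus O? | Is it a listed primary outcome? |
|---|---|---|---|
| Abstract, primary aim | W vs O, all patients | Yes | No |
| Main Discussion | W vs O, raised D-dimer | No | Only roughly (item 1 without the split) |
| Primary outcome 1 | RW vs NRO vs RRO | No | Yes |
| Primary outcome 2 | RO vs NO, within Group O | No | Yes |
| Sample size | RW vs RNO plus RRO | No | No |

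By the article's own code, RNO plus RRO is everyone in Group O who is raised *off* treatment. It takes in patients normal at randomisation (RNO) and leaves out patients raised at randomisation (NRO). The raised-at-randomisation part of Group O is NRO plus RRO.

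**2. Reproducing the sample size**

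Inputs (Sample size section): p1 = 0.214, p2 = 0.043, alpha 5% (taken as two-sided), power 90%. With p̄ = 0.1285:

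n = [1.960·√(2·0.1285·0.8715) + 1.282·√(0.214·0.786 + 0.043·0.957)]² / 0.171²
= [1.960·0.4733 + 1.282·0.4576]² / 0.02924 = 78.4, so **79** per group.

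Then 79 × 2 × 2 / 0.9 = 351.1, so 352 entered, and 79 × 4 = 316 completing. Both match the article. At two-sided 2.5% the same formula gives 92.8, so 93 per group.

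**3. Reproducing the W versus O power**

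158 per arm (316/2), Group O 14.2%, two-sided 5%:

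- W 4.3%: power 86.3%
- W 1.4%: power 99.1%

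These match the stated 86 to 99%. At 2.5% they would be 79.0% and 98.0%, so the stated range reproduces only at an undivided 5%. Primary outcomes 1 and 2 have no stated alpha or power.

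**4. Chance of at least one false positive if each contrast were tested at 5%**

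Simulation, 400,000 trials per scenario. Per arm: 79 raised and 79 normal at randomisation. One common recurrence risk of 10%, 14.2% or 21.4%. The share of Group O keeping the same D-dimer class off treatment is 50% or 70%. The common risk and this share are assumptions. Outcome 1 is one three-group chi-square test. The sizing contrast is read as RW vs NRO plus RRO.

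| Tests | At least one false positive |
|---|---|
| Two listed primary outcomes | about 9% |
| W vs O, and RW vs NRO plus RRO | about 8.5% |
| All four contrasts | about 14.5% |

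The assumed inputs moved these by less than one percentage point. Four independent tests would give 1 − 0.95⁴ = 18.5%. The true figure is lower because the contrasts share patients.

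**5. How often the two statements of the main question would disagree**

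Scenario A: Group O risk 14.2% whatever the D-dimer, Group W 4.3%. W versus O is significant in 88% of simulated trials and RW vs NRO plus RRO in 60%. W versus O succeeds while the raised-D-dimer contrast fails in about 29%.

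Scenario B: Group O risk 21.4% if raised at randomisation and 7% if normal (mean 14.2%), Group W 4.3%. W versus O is significant in 88%. Both contrasts succeed in 86%, so that split is about 2%.

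The simulated 88% is a little above the formula's 86.3% because the formula is a normal approximation.

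**The case against.** The strongest reply is that this is a condensed article, and that testing order and multiplicity control belong in an analysis plan that is not shown. That stands for those details. It does not cover incompatible statements of the main question: condensing a text explains omissions, not conflicts.

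It is also fair that primary outcome 1, the apparent intent of the sample size and the main Discussion all point towards raised-D-dimer patients. They differ mainly in how Group O is grouped. This makes the repair easier, but it leaves the abstract's primary aim outside the primary outcomes and the sample-size label at odds with its own coding.

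Three stronger readings are tempting and are not supported.

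- A reader might infer that every contrast may be claimed at a full 5%, so that success on any of them makes the trial positive. The article gives an alpha only for the sizing test. For W versus O the 5% is shown by reproduction. For the two listed outcomes it would be inferred from silence.
- A reader might push the false-positive chance to about 19% by adding all pairwise versions of outcome 1. That counts largely the same raised-D-dimer comparison more than once.
- A reader might note that in Scenario A, W versus O and RO versus NO give different results in about 86% of trials. That is no conflict: warfarin works and D-dimer does not predict, so both questions are answered correctly.

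Pooling RO versus NO with treatment contrasts in one error family is itself debatable, since it supports a different kind of claim. The figure confined to treatment effects is the 8.5%.

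**Conclusion.** The contradiction is real and lies in the current text. The sample-size arithmetic is correct; what is unclear is which comparison it serves. Conditional on each contrast being tested at 5%, the false-positive chance is 1.7 to 2.9 times nominal (8.5/5 to 14.5/5), given the assumed null risk of 10 to 21% and D-dimer concordance of 50 to 70%. The practical consequence depends on the truth: the split between the all-patient and raised-D-dimer answers is about 29% if D-dimer is not prognostic and about 2% if risk is concentrated in raised-D-dimer patients. This should be corrected. It does not show that the design fails.

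**What to change.** Name one deciding comparison at two-sided 5%, and align to it the aim (abstract and main Discussion), the primary outcomes and the sample-size contrast.

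The choice most consistent with the 79 per group is RW versus NRO plus RRO, that is, all patients raised at randomisation compared by arm. It keeps a randomised comparison, and it fits the single 50% positive rate applied to both arms. The sample-size label would then be corrected from RNO plus RRO. The sponsor should confirm the intent.

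Make the other contrasts secondary, or place them in an order or alpha split that the sponsor states in advance. Report RO versus NO as a separate prognostic question.

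**Cost:** wording only. No patients are added, and the deciding test keeps its 90% power (90.2% with 79 per group). By contrast, splitting alpha equally over two tests would cut that to 84.2%, or need 93 per group (93 × 4 / 0.9 = 413.3, so 414 entered).

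The downside should be stated: contrasts not named as deciding lose confirmatory status or power. If W versus O is tested only after the raised-D-dimer test succeeds, its confirmatory success falls from about 88% to 86% in Scenario B, and to about 59% in Scenario A. A sponsor who regards the abstract's all-patient aim as the main question may therefore prefer a different order.

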**Trial registration:**

ISRCTN73819751

## Background

Venous thromboembolism (VTE) is associated with significant mortality and morbidity, including post-thrombotic syndrome (PTS). VTE is considered as a chronic disease with pulmonary embolism (PE) and deep vein thrombosis (DVT) being different manifestations of the same disease process.

Currently, patients with a first episode of unprovoked proximal DVT or PE, with no apparent other risk factors for recurrent VTE, are given a course of oral anticoagulation (warfarin in the UK) treatment which is then discontinued. The optimum duration of warfarin therapy depends on the individual patient and has not been defined [1]. Concern in terms of duration of treatment is due to the risk of bleeding from prolonged warfarin treatment. Several studies have investigated the optimal duration of anticoagulant therapy with the British Committee for Standards in Haematology (BCSH, 1998) recommending between six weeks and six months, depending upon the aetiology [2,3].

A substantial proportion of patients – up to 17% [4-7] go on to have a recurrent episode of VTE which can be a potentially life-threatening condition [8]. If recurrence occurs, the patient is normally managed thereafter with long-term warfarin, provided there are no contraindications. Although optimal duration of anticoagulation treatment for patients with a first idiopathic VTE remains uncertain, randomised trials have suggested that patients should be treated for a minimum of three months [9] but beyond that the duration of anticoagulation has little effect on the rate of recurrence^3^. There is an annual recurrence rate following a first VTE of approximately 10% per annum following treatment cessation, irrespective of the duration of warfarin therapy [10]. This suggests that some patients with a first unprovoked VTE should continue warfarin in the long-term however we are currently unable to identify this population. Studies of extended treatment with low dose warfarin have confirmed that maximal benefit is conferred at standard therapeutic targets rather than fixed low dose regimes [11,12].

It would be very useful to have an accurate predictor of recurrence of VTE to decide which patients with a first episode of unprovoked proximal DVT or PE would be most likely to benefit from long term oral anticoagulation, and also which patients should only receive short term therapy.

D-dimer is a fibrin degradation product, present in the blood after a blood clot is degraded by fibrinolysis and levels of D-dimer can be tested using laboratory and point-of-care (POC) testing devices. The primary clinical use of D-dimer testing has been in conjunction with probability scores to determine whether further investigation is required for the diagnosis of VTE. More recently interest has been shown in studies which have investigated whether D-dimer can be utilised as a guide for determining who is at risk of recurrent VTE following treatment of the initial acute episode [13,14].

Previous small studies outside the UK have suggested that D-dimer levels could act as a useful predictor of recurrent thromboembolism in patients whose warfarin is discontinued [14-16]. There are limited data on utility of the D-dimer as a predictor in patients still on therapy, but Rodgers *et al.* have shown that D-dimer can be used to predict recurrence in low risk female patients [17]. In addition to D-dimer levels a recent meta-analysis has suggested that age and gender may be effective in predicting recurrent VTE [18]. This study concluded that men are at greater risk of developing a recurrent VTE after a first unprovoked episode and that age could be used as predictor in women. Therefore D-dimer levels could be a potentially useful clinical tool to decide which patients, with a first episode of unprovoked proximal DVT or PE, would most likely benefit from long-term warfarin therapy.

The conclusions of 2 systematic reviews of D-dimer testing after stopping treatment for VTE, (7 studies with a total of 1888 patients) were: “additional research is needed to establish the optimal interval between stopping anticoagulation and performing D-dimer testing, to identify the optimum cut-off that predicts recurrence and to develop a clinical prediction rule for recurrent DVT.” [19], and “strategies which incorporate a number of high performing baseline and post-baseline predictors could be more effective in predicting recurrent VTE and should be tested. If oral anticoagulation is continued, there is no evidence on the duration of this extended therapy [20].”

The only UK data included in these reviews were from a prospective cohort study of 272 patients with a first episode of venous thrombosis that was unprovoked or provoked by a non-surgical trigger. They undertook D-dimer testing 1 month after cessation of warfarin therapy and found a non-significant difference in recurrence (5.5/100 patients years in D-dimer + ve *vs.* 4.1/100 patient years in D-dimer –ve) [10].

PTS is a frequent and costly complication of DVT which can lead to chronic venous insufficiency and ulceration. PTS has a cumulative incidence after 2 years of around 25% and it has been postulated that prolonged treatment with oral anticoagulants could prevent the development of PTS [21]. The only data available from a randomised trial suggested no association between long-term low dose warfarin treatment and development of PTS [22]. The prevalence of PTS in this study was 37% after 2.2 years, with severe PTS in 4%. A recent study demonstrated an association between D-dimer level and the development of PTS [23], this is something that will be investigated during the course of this study.

## Methods

### Aims and objectives

Considering patients with a first unprovoked proximal DVT and PE who have been treated with 3–6 months oral anticoagulation, the aims of the study are:

•To investigate the effect of extending treatment with oral anticoagulation in terms of reduction in incidence of VTE and PTS

•To develop an algorithm to predict high/low recurrence rates in these patients

As part of this we will be investigating the following:

•To establish the performance characteristics of D-dimer testing whilst still on treatment as a prediction tool for recurrence of VTE in patients with first unprovoked proximal DVT or PE.

•To establish factors which contribute to the recurrence of VTE in patients with a first unprovoked proximal DVT or PE.

•To determine the cost-effectiveness of the measurement of D-dimer and subsequent extended treatment with anticoagulation.

•To determine patient preferences and utilities with regard to extended warfarin treatment.

### Participants

Patients will be recruited through a number of primary care and secondary care anticoagulation clinics in the wider Midlands area over a two year period.

Patients identified as receiving warfarin for a first unprovoked proximal DVT or PE and who are eligible for the trial (Table 1) will receive a brief information sheet about the study during their anticoagulant clinic appointment. They will also be given a post card to return to the research department stating their willingness in principle to take part in the study, for their GP to be contacted and their records to be accessed for the purpose of checking their eligibility for the study. The patients GP will simultaneously be sent a summary of the trial and informed that one of their patients wishes to participate. The GP will be asked to complete a form to state whether they wish their practice to take part in the study.

**Table 1 T1:** Study inclusion and exclusion criteria

**Inclusion criteria**	People aged 18 years or over with a diagnosis of first unprovoked^*^ proximal^** ^DVT or PE on treatment with anticoagulants
	Have completed 3 – 6 months of anticoagulant therapy (target 2–3)
	^*^The episode will be defined as unprovoked as long as there is no history within the previous 3 months of:
	major surgery; lower limb trauma e.g. fracture, cast, limping for 3 days; use of the combined oral contraceptive pill or hormone replacement therapy ; pregnancy; significant immobility e.g. confined to bed for 3 days; active cancer.
	^**^Proximal refers to a DVT alone in the trifurcation area, popliteal, superficial femoral, deep femoral, common femoral and iliac veins.
**Exclusion criteria**	Patients under the age of 18 years
	Patients with another indication for long term warfarin therapy e.g. Atrial Fibrillation
	Patients with a diagnosis of first unprovoked proximal DVT or PE who are no longer on anticoagulation therapy
	Patients with a high risk of bleeding as evidenced by any of the following:
	• Patients with a previous episode of major bleeding where the cause was not effectively treated
	• Known thrombocytopaenia with a platelet count of less than 120 ×10^9^ /L
	• Known chronic renal failure with a creatinine of more than 150 μmols/L (1.7 mg/dl) or eGFR less than 30
	• Known chronic liver disease with a total bilirubin of more than 25μmols/L (1.5 mg/dl)
	• Active peptic ulcer
	• Patients requiring antiplatelet therapy (eg Aspirin and/or Clopidogrel)
	Patients with a vena cava filter in place
	Patients who have had a D–dimer test performed within 2 months of potential enrolment other than for evaluation for suspected recurrent VTE that was not confirmed
	Patients whose GP expects their life expectancy to be less than 5 years
	Patients unable to attend follow up visits due to geographic inaccessibility
	Patients participating in a competing investigation
	Patients with known antiphospholipid syndrome
	If patients are subsequently found to have antiphospholipid syndrome then they will have to be excluded.
	Patients with known inherited protein C and/or protein S or antithrombin deficiency
	If patients are subsequently found to have protein C and/or protein S or anithrombin deficiency then they will have to be excluded.
	Patients with a diagnosis of active cancer
	Patients unwilling to give consent

Those patients who reply with a positive response from willing general practices will be contacted to determine that they still wish to take part in the study. If still willing to take part then the research nurse or a member of the practice staff will access the patients’ primary care notes to assess their eligibility for inclusion into the study. If the patient is eligible then they will be followed up (at least 1 month before the end of their current treatment) to arrange their first visit to the GP surgery. Any additional travel costs and prescription costs will be paid to the patient from study funds.

Those with a negative reply will not be contacted. Those patients who do not return their postcard will be given a second postcard a month after the first one was given out. If a patient wishes to take part in the study but their GP is unwilling, alternative arrangements will be made at a hospital clinic.

The first appointment at the GP clinic will inform as to the nature of the trial. For those patients willing to participate the research nurse will obtain written informed consent.

